### **C. Sample size, statistical methods, and power calculation**

1. Descriptive statistics (frequency/percent and mean/SD) will be mainly used to summarize participants' characteristics and intervention outcomes. The means and 95% CIs for pre-post changes in the primary (i.e., frailty index) outcome will be estimated. No imputation will be considered for missing data. The Wilcoxon rank sum test will be used for comparing the pre-post changes in frailty index between the two groups. The intervention will be considered feasible if the retention rate and the proportion of completed sessions are more than 80%. Pre-generated randomization codes will be prepared by the biostatistician ([name]). The randomization ratio will be 1:1.
2. [name], who will be the assessor for the study assessments, will be blinded to which group the participants have been allocated to. Participants will be aware of which group they are in. The study coordinator and [name] will have access to the code to the blind. The code will not need to be broken unless there are unforeseen circumstances in which [name] needs to know which group a particular participant was assigned to. Following the baseline assessment (visit 2), participants will be randomized to one of the two groups based on pre-generated randomization codes prepared by the biostatistician, [name]. In accordance with the CONSORT guidelines, sequence generation, allocation concealment and group allocation will be blinded and separate processes.
3. For this pilot study, we plan to enroll a convenience sample of 60 ambulatory people (30 per group) with Multiple Sclerosis living with frailty that meet inclusion/exclusion criteria. These subjects will provide feasibility data and preliminary efficacy data for designing a future study if the findings are promising. We expect a 15% dropout rate, and at that at least 24 subjects per group will complete the study.

**D. Subject Criteria (See Vulnerable Populations appendix, if applicable):** We will enroll 60 ambulatory pwMS living with frailty. During Visit 1, we will screen subjects for frailty based on established cut-offs according to the Fried phenotype. This screening tool was chosen to ensure a time- and cost-effective identification of pwMS who are frail.

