1. Inclusion criteria: Subjects must be aged 40-65 years old to be enrolled in this study. Subjects must meet 3 of 5 Fried's criteria (weight loss; fatigue; weakness; ambulation; inactivity) to be considered. Subjects must have a confirmed diagnosis of MS by the treating neurologist, be free from MS relapses in the last 30 days, have an Expanded Disability Status Scale (EDSS) score  $\leq 6.0$ , and be fluent in spoken and written English.
2. Exclusion criteria: Subjects will be excluded from participation if they are unable to walk unassisted for at least ten meters, are diagnosed with other clinically important neurological conditions (such as Parkinson's Disease, epilepsy, etc.), exhibit severe cognitive impairment (as determined by a Mini-Cog score  $<3$ ), and are diagnosed with active psychiatric problems. Additional exclusionary factors include unstable cardiovascular conditions (e.g., malignant arrhythmias, critical mitral stenosis, clinically severe left ventricular outflow obstruction, critical proximal coronary artery stenosis), arthritis of the lower limbs, acute lower back or lower limbs pain, rheumatic and/or severe orthopedic problems that may interfere with resistance training. Co-I [name]

will confer with the research team to ensure that the inclusion/exclusion criteria are adequately implemented.

3. **Withdrawal/Termination criteria:** Participants could be withdrawn from the study due to a variety of circumstances. Participants may be withdrawn if they develop a condition deemed exclusionary. Participants may be withdrawn from the study if the PI, and/or the study team deem that it is in the participant's best interest to be withdrawn, or if a significant safety concern has been identified. If there are any concerns that the participant and/or study team will be at risk if the participant continues, they will be withdrawn. Some participants initiate withdrawal based on physical health or availability, or other personal choices.
4. Subjects currently enrolled in other exercise trials will not be considered eligible to participate.

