#### F. Risk/benefit assessment:

1. **Physical risk:** The main risk of this study would be risks typically associated with exercise. Participants may experience shortness of breath, muscle soreness, dizziness, and increased heart rate. These effects typically resolve shortly after the exercise is stopped, however, muscle soreness may last a few days. Given the prevalence of fatigue in persons with MS, it is possible that participants will become fatigued during study visits. Additionally, the blood draw may present a risk to participants. Participants may experience momentary discomfort and bruising. Infection, excess bleeding, clotting and fainting are also possible although their occurrence is unlikely. Participants may also be at risk of falling during the exercise training. Injuries sustained from falling could range from mild, such as scratches and bruises, to severe, such as head injuries and/or bone fracture. There is also the risk of a data breach or unintentional disclosure, which is a risk to a participant in ANY research study. There is a risk of contracting COVID-19, which is also present in any research which involves face-to-face interaction between humans. Finally, the pressure pain threshold test may be uncomfortable for some individuals.

The first risk identified was the risk of incurring symptoms typically experienced during exercise. This risk will be mitigated in a variety of ways. Participants will be allowed breaks whenever they need it and be given access to water. Participants will only be

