- b. Furthermore, the Principal Investigator (PI) will be responsible for ensuring participants' safety on a daily basis. Trained research personnel will perform monitoring weekly to assess for data entry errors, outliers, and missing data. Personnel will also perform audits quarterly to assess adherence to the protocol, informed consent documents, source documents, regulatory documents, signature lists, site delegation authority lists, screening lists and enrollment logs. The appointed study monitor will sign the monitor log and submit a monitor report to the PI. The research personnel will use multiple techniques to minimize missing data, losses to follow up, and non-response bias. In summary, the investigators will ask participants to provide primary and back-up contact information. In addition, the protocol permits assessment of outcomes telephone survey, and postal survey if the participant declines a face-to-face visit. The investigators will create Standard Operating Procedures for electronic data entry, data access, data back-up, and data security.
2. The investigators will use the definitions for "Adverse Event" and "Serious Adverse Event" as defined by the International Council for Harmonization. Data from the study will be monitored on a continuous basis by the PI, and co-investigators. All serious adverse events (SAEs), adverse events (AEs), will be reviewed by the PI on an ongoing basis. Participants will be encouraged to report any discomfort or adverse outcomes they experience during each study visit. Trained research assistants will record any AE/SAE during the intervention. The study team will report SAEs and AEs to the PI as soon as possible.
3. Research personnel will ascertain adverse events from the participant by non-directive questions during the research visits. In addition, participants may voluntarily report

adverse events. Research personnel will record adverse events on the case report form. The investigators will score the adverse event in terms of:

Severity: mild, moderate, or severe.

Clinically significant: yes or no.

Requires therapy: yes or no.

Relationship to the experimental interventions: suspected or not suspected.

Duration of the adverse event: start date, end date, or ongoing at visit.

Serious adverse event: yes or no.

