When research personnel learn that a participant has experienced an adverse event, research personnel will contact the PI on the same day to receive instructions for the transfer of the participant for treatment and follow-up of the adverse event. In addition, research personnel will complete an adverse event form. Participants with adverse events are eligible to remain in the trial unless there is withdrawal of consent. Participants who have experienced a serious adverse event will be withdrawn from the study.

The investigator will communicate with the participant and primary care physician (if deemed necessary by PI) to acquire information to complete the treatment questions on the adverse event form. The specific questions are: no action taken (i.e., further observation only); intervention temporarily interrupted; intervention permanently discontinued due to this adverse event; patient hospitalized. The investigator will continue to communicate with the participant and primary care physician until resolution to record change of severity, change of suspected attribution to intervention, and change of treatments for the adverse event.

The investigators and the Data and Safety Monitoring Board will review Adverse Events and Serious Adverse Events. If unexpected experimental-related adverse events emerge during the course of the trial, then the investigator will report the adverse events to the Institutional Review Board and the National Institutes of Health within the timelines required by each entity.

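### Section II.D.3 requires withdrawal for any risk concern and does not separate stopping training from leaving the study, so an exercise participant stopped without an adverse event could be lost to the Aim 2 comparison

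*Protocol*

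**What the plan says.** Protocol II.D.3 (Withdrawal/Termination criteria) is about withdrawal from the study. It lists grounds on which the team has discretion: a new exclusionary condition, the participant's best interest, "or if a significant safety concern has been identified". The next sentence is mandatory: "If there are any concerns that the participant and/or study team will be at risk if the participant continues, they will be withdrawn".

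II.L.3 treats adverse events differently: "Participants with adverse events are eligible to remain in the trial unless there is withdrawal of consent". Its form records what happened to the intervention separately, including "intervention permanently discontinued due to this adverse event". A serious adverse event does lead to withdrawal from the study; that rule is outside this point.

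Three other provisions bear on the consequence:
- II.C.1 compares pre-post change in the frailty index between groups and states "No imputation will be considered for missing data".
- II.L, item b, describes remote follow-up: "the protocol permits assessment of outcomes telephone survey, and postal survey if the participant declines a face-to-face visit".
- III.G pays someone who drops out or withdraws only for visits already attended.

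**The concern.** The looser trigger carries the stronger consequence. A significant concern leaves the team a choice, while any concern at all removes it. II.D.3 also does not say whether continuing means continuing to train or continuing in the study, and withdrawal from the study is the only outcome it offers.

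The two are not the same for the analysis. A participant who is off training but still in the study can give a Visit 3 frailty index and be analysed as randomized. One who is withdrawn probably cannot. Before Visit 3 only the exercise arm trains, over 18 supervised sessions, and II.F.1 names a training hazard: "Participants may also be at risk of falling during the exercise training". The waitlist arm has no comparable occasions for concern. Any such losses would therefore fall mainly on one arm, plausibly among those who tolerate training least. The Aim 2 effect estimate, which the protocol wants for planning a full trial, could then look somewhat better than it should.

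**Working it through.** **1. The plan's own figure.** II.C.3 states "We expect a 15% dropout rate, and at that at least 24 subjects per group will complete the study". Check: 30 × (1 − 0.15) = 25.5 completers per group, consistent with at least 24. The planned loss is thus 30 × 0.15 = 4.5 to 30 − 24 = 6 per group. The sample is one of convenience, so there is no power calculation to reproduce.

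**2. The rules side by side.**

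| Situation | Section | Consequence |
|---|---|---|
| Cannot walk 15 minutes | II.E.2 | Shorter bouts, built up |
| Pain score above 3 | II.F.1 | That session stops |
| Non-serious adverse event | II.L.3 | May remain; intervention status recorded separately |
| Significant safety concern | II.D.3 | May be withdrawn from the study |
| Any concern of risk | II.D.3 | Must be withdrawn |

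No row covers training stopped permanently, without an adverse event, while the participant stays in. That is the gap.

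**3. Would Visit 3 be lost?** No section schedules Visit 3 after withdrawal by the team. The remote route is worded for someone who declines a visit. Even if it were used, at least 6 physical-performance items + 12 biomarker items = 18 of the 70 in Table 1 need attendance, so it could give a partial index at most. Loss of a full index is an inference, but a fair one.

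**4. Effect on the exercise-arm mean.** The protocol gives no removal rate. Assume k = 1 to 3 of 30 exercise participants are removed, that they would have shown no change, and that the other 30 − k are observed with mean reduction m.
- All-randomized mean = m(30 − k)/30; relative overstatement = k/(30 − k).
- k = 1: 1/29 = 3.4%. k = 2: 2/28 = 7.1%. k = 3: 3/27 = 11.1%.
- At m = 0.030 the shift is 0.030 × k/30 = 0.001, 0.002 or 0.003.
- Standard error, with an assumed SD of change of 0.05 to 0.10: 0.05/√29 = 0.009 to 0.10/√27 = 0.019.

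The shift is small against the standard error. It would alter a conclusion only close to the 0.03 threshold for clinically meaningful change. For example, 0.032 with two unchanged participants restored is 0.032 × 28/30 = 0.0299.

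**5. Effect on the Wilcoxon test.** Simulation with no true effect, 30 controls, normally distributed changes and an assumed two-sided 5% level. The table gives the chance of a significant result favouring exercise, which is about 2.2% to 2.5% with nobody removed.

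| Who is removed (assumed) | k = 1 | k = 2 | k = 3 |
|---|---|---|---|
| Those nearest no change | 2.5% | 2.5% | 2.3% |
| At random from the worse half | 2.9% | 3.8% | 4.7% |
| Exactly the worst | 4.3% | 6.7% | 10.2% |

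The inflation comes wholly from the assumption about who is removed. Under the no-change assumption of step 4 there is none.

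**6. Retention.** II.B defines it as participants completing the intervention over those enrolled at baseline. A participant whose training is stopped for good is a non-completer whether or not they stay for Visit 3, so retention is the same either way.

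**The case against.** The best defence is that the protocol already responds to risk in steps short of withdrawal. Under II.F.1 participants do only exercises they are comfortable with, the programme is individualized and readjusted every two weeks, and they are spotted and wear a harness. Pain above 3 ends only that session, and II.E.2 lets walking build up in 1 to 3 minute bouts. This stands, and it narrows the point: many tolerance problems will never reach II.D.3. None of these provisions covers a permanent stop.

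Second, the two triggers can be read as different things, one a concern already identified and the other forward-looking risk to participant or staff. That is a possible reading, but a significant safety concern will nearly always imply some risk in continuing, so the mandatory sentence still overtakes the discretion.

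Third, II.L commits staff to several techniques to limit missing data and loss to follow-up, and II.F.1 reports no serious adverse events among 108 people in the related virtual-reality programme. Both suggest that losses may be few. But the first does not say that a withdrawn participant is brought back, and the second counts serious events, not risk-based stops. That programme also did not select for frailty (I.B.3).

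A reader might go further and infer any of the following, which the document does not support:
- that II.D.3 forbids Visit 3 after withdrawal; it is silent;
- that the Wilcoxon test's false-positive rate in favour of exercise will rise to as much as 10%; this needs those removed to be exactly the worst outcomes, and nothing in the protocol says so;
- that the 80% retention criterion is put at risk; the definition in II.B makes it insensitive to this rule;
- that stopping decisions must be taken from the PI because the PI codes the index blinded; II.L makes the PI responsible for daily safety, and this fix does not need that change.

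**Conclusion.** The point holds in limited form. II.D.3 contains an inverted pair of thresholds and, outside adverse events, does not distinguish a permanent stop of training from leaving the study. The participants concerned are those stopped for good without an adverse event. If any are withdrawn, they probably drop out of the Aim 2 frailty comparison, mainly from the exercise arm.

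The wording problem is certain, its numerical effect is not. The size in step 4 rests on an assumed 1 to 3 removals and an assumed absence of change in those removed, and is well within sampling error. Severity is minor to moderate. It is worth correcting because the bias would run in a predictable direction, the effect sizes are meant to inform a larger trial, and the remedy is cheap.

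**What to change.** In II.D.3, replace the separate grounds for team-initiated removal (risk, significant safety concern, best interest, new exclusionary condition) with one rule:

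> If continuing training is judged unsafe or not in the participant's interest, training will be interrupted or permanently stopped. The participant remains in the study and attends Visit 3 as scheduled unless consent is withdrawn or the Visit 3 procedures themselves would put the participant or staff at risk; any Visit 3 procedures that are safe will still be done.

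All four grounds must be covered. If only the risk sentence were changed, the same participant could still be removed on best-interest grounds or for a new exclusionary condition. Protection is not weakened, since unsafe training still stops. The PI's safety responsibility and II.L.3, including its serious-adverse-event rule, stay as they are.

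The cost is one amended section and one additional Visit 3 per participant concerned: $50 (III.G), about 90 minutes of testing and a blood draw (II.E.2). For 1 to 3 participants that is $50 to $150 and 1.5 to 4.5 hours. The frailty result may also be less favourable.

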#### **E. Specific methods and techniques used throughout the study**

1. **Laboratory tests:** Participants will be asked to complete a blood draw, in fasting conditions (in the morning), during study visits 2 and 3. The blood draws will be performed by a trained nurse at the Landon Center on Aging. The blood drawn will be done to assess biomarkers that are correlates of frailty such as NfL, BDNF, GFAP, CRP, IL-6, IL-10, TNF-alpha, IFN-gamma, and CXCL9, mi-RNAs. The amount of blood drawn will be approximately 12-15 mL.
2. **Study Procedures:** Participant involvement in this study will begin with the screening visit, where subjects will be screened for eligibility using objective diagnostic criteria. The screening visit will take place at the KU Center for MS Care and will take about 10-15 minutes. At the screening visit, participants will go through the informed consent with a study team member. If the participants consent, they will then complete the Mini-Cog questionnaire and the Fried phenotype to determine if they meet the frailty criteria. The Fried phenotype evaluates 5 components: fatigue, weakness, ambulation, inactivity, and loss of weight. Fried scores range from 0-5 (i.e., 1 point for each component). Higher scores reflect higher frailty. Subjects who total at least 3 points out of 5 will be classified as frail and will be eligible to participate. The Fried phenotype will also be repeated after the intervention, during Visit 3.

Once participants meet the screening criteria, they will attend the first study assessment (Visit 2 – baseline assessment). During this visit, participants will undergo the blood draws in the morning, in fasting conditions (i.e., at least 12 hours of fasting), at the Landon Center on Aging (laboratory tests listed in Table 1 – see biomarkers). After the blood draw, participants will complete a comprehensive battery of physical and cognitive tests, self-reports, clinical measurements, and nutritional status measures (see Table 1) in the Human Performance Laboratory at the Landon Center on Aging. These procedures will take about 90 minutes. At the end of the visit, they will be provided with a wearable sensor consistent with our previous work. From these assessments, we will derive 70 health-deficit items that will be used to calculate a frailty index according to the guiding principles of the deficit accumulation model. A synopsis of the frailty index is provided in Table 1. The health-deficit items will be coded on a 0-1 scale, to indicate the absence or presence of health deficits, using standard validated procedures by a single researcher experienced in frailty assessments and blinded to group allocation (PI [name]). The frailty index score will be calculated as the

sum of all deficit-related scores divided by the sum of the total number of possible health deficits. The same procedures will be repeated during the post-intervention assessment (Visit 3). During the screening visit and visit 3, participants will complete two pain questionnaires and a pain threshold test. First, participants will complete the Paindetect, a screening tool of neuropathic pain (one of the most common pain pwMS) and the Fibromyalgia Survey Criteria (a proxy measure of nociplastic pain). Then, participants will undergo a pressure pain threshold involving the middle part of bulk of medial and lateral gastrocnemius muscles as well as the thumbnail of the participant's dominant hand. This is measured with a digital algometer, which has been shown to have good reliability in the gastrocnemius region. The digital algometer is made up of a 1-cm-wide disk located on the middle part of bulk of medial and lateral head of gastrocnemius muscles. The algometer's pressure will be increased gradually (with a speed approximately 1 N/cm^2 per second) and will be stopped immediately when the participant reports the transition from discomfort to pain. The average value of three measurements will be recorded.

**Table 1.** Synopsis of the 70-item frailty index: Domains, sources and measures utilized as health deficit items.

| Domains of frailty             | Items, number | Sources                                           | Measures                                                                                                                                                                      |
|--------------------------------|---------------|---------------------------------------------------|-------------------------------------------------------------------------------------------------------------------------------------------------------------------------------|
| Global health                  | 2             | MSQoL-54                                          | self-reported health.                                                                                                                                                         |
| Function in ADLs               | 6             | MSQoL-54                                          | Questions about the ability to perform ADLs                                                                                                                                   |
| Energy                         | 5             | MSQoL-54, MFIS                                    | Questions about tiredness, energy, and fatigue                                                                                                                                |
| Psychosocial function          | 6             | MSQoL-54, MFIS                                    | Questions about participation in social activities, feelings of happiness, downheartedness, etc                                                                               |
| Health attitudes/sleep quality | 6             | Wearable sensor (worn for three consecutive days) | Number of daily steps, number of 30-seconds walking bouts, moderate to vigorous physical activity, total physical activity, number of hours spent sleeping, sleep efficiency. |
| Cognition                      | 6             | CVLT-II, SDMT, BVMT, TMT, MFIS                    | Total words recalled, Total BVMT score, Raw SDMT score, TMT times, self-reported memory problems.                                                                             |
| Physical performance           | 6             | Instrumented gait analysis, 6MWT, Dynamometry     | Self-selected gait speed, functional ambulation profile, 6MWT distance, handgrip strength, knee extensor strength, 5X chair stand.                                            |
| Nutritional status             | 5             | Laboratory tests, Self-report.                    | BMI, serum albumin, appetite disorders, problems with cooking.                                                                                                                |
| Comorbidities                  | 16            | Medical records, Automated BP monitor, MSQoL-54.  | Polypharmacy, systolic BP, diastolic BP, comorbidities; fall history                                                                                                          |
| Biomarkers                     | 12            | Laboratory tests                                  | NfL, BDNF, GFAP, CRP, IL-6, IL-10, TNF-alpha, IFN-gamma, and CXCL9, mi-RNAs.                                                                                                  |

**Legend:** ADL: activities of daily living, MSQoL-54: 54-item multiple sclerosis quality of life questionnaire, MFIS: modified fatigue impact scale, CVLT-II: California verbal

learning test, SDMT: symbol digit modalities test, BVMT: brief visuospatial memory test; TMT: trail making test, 6MWT: 6-minute walk test, BP: blood pressure, BMI: body mass index, CRP: c-reactive protein.

All study outcomes will be assessed in a standardized manner during Visit 2 and 3. Following visit 2, participants will be randomized to one of the two groups based on pre-generated randomization codes prepared by the biostatistician. In accordance with the CONSORT guidelines, sequence generation, allocation concealment and group allocation will be blinded and separate processes. Participants will then either complete the waitlist period (passive control) or attend the exercise training visits 3 times a week, for 6 weeks, totaling 18 training visits. Each training visit will last one hour. The training visits will take place at the Laboratory for Advanced Rehabilitation Research in Simulation at the University of Kansas Medical Center.

**Intervention (Multimodal exercise) Group:** Participants will complete 15 minutes of virtual reality treadmill training (VRTT), followed by 30 minutes of progressive evidence-based resistance training (RT), followed by other 15 minutes of VRTT. This interval training design was chosen to induce acute fatigue before the last bout of VRTT. See Table 2.

**Table 2.** The Multimodal exercise program.

| Exercise components      | Duration   | Description                                                                                                                    | Target (frailty domains)*             |
|--------------------------|------------|--------------------------------------------------------------------------------------------------------------------------------|---------------------------------------|
| 1) VR treadmill training | 15 minutes | Treadmill walking with interactive virtual environment.                                                                        | - Slowness
- Cognition             |
| 2) RT                    | 30 minutes | Seated leg press, seated hamstring curls, seated calf raises, seated chest press, seated lat-pulldowns, seated shoulder press. | - Muscle weakness
- Shrinkage      |
| 3) VR treadmill training | 15 minutes | Treadmill walking with interactive virtual environment.                                                                        | - Slowness, Cognition
- Exhaustion |

**Legend:** VR: virtual reality, RT: resistance training, \* The multimodal exercise program will also inherently target the 'inactivity' component of frailty.

Both the VR and RT components of the program will be individualized based on the participant's abilities and the training progression will be adjusted every 2 weeks. Over-ground gait speed will be assessed prior to the intervention and every two weeks thereafter and will be utilized to set the treadmill speed for the VR component. As part of VR, participants will navigate through a virtual environment projected on a TV screen while receiving feedback from the system (Figure 2). The RT component will consist of performing evidence-based RT exercises, as fully described in Table 2. In the event participants are unable to complete 15 minutes of continuous walking, walking duration will be progressively increased in 1–3-minute bouts until the prescribed time is reached. The estimated 1-repetition maximum (1-RM) of all RT exercises will be evaluated using validated standard procedures (for untrained individuals) prior to the intervention. At the beginning of the intervention, participants will complete 3 sets of 8-12 repetitions at 20-30% of the 1RM and slowly progress up to 80% over the course of 8 weeks. The end point of each set will always be limited to volitional fatigue. Recovery periods of 2-4 minutes will be prescribed between sets and exercises.

**Control Group:** Participants randomized to the control group will be put on a waitlist (passive control group) for 6 weeks. Upon completion of Visit 3, participants in the control group will be able to receive the intervention, if they wish so.

[figure not shown]

Panel A

[figure not shown]

Panel B

Figure 2. Gait Better (TM) virtual reality (VR) treadmill training set up. Panel A. Camera detects markers on feet and projects them on screen. Panel B. View of VR monitor depicting individual's virtual feet, visual distractors, and obstacles.

3. All procedures, tests, and study visits will be performed solely for research purposes. Therefore, participants and their insurance companies will not be billed.
4. The blood samples taken in the study will be labeled with the participant's study ID as a way of maintaining confidentiality, so the blood sample will not be traceable to the participant's name. The blood sample will be destroyed by researchers after the participant's involvement in the study is complete and data have been analyzed. The blood samples will be stored in a secure area in Breidenthal.
5. Timeline: This project will be completed in 2 years. In months 0-2, we will obtain IRB approval, prepare case report forms and train staff. The study will begin in month 2. For a given participant the study will take 2.5 months. We will aim to recruit and train 7-8 participants in 4-month cycles starting in month 2. All participants will have completed training and the post-intervention assessment (month 18) after 4 cycles (4 cycles x 7-8 participants ~ 30 participants). This approach will yield a 6-month buffer to allow for unanticipated delays. Analyses of the unblinded data and preparation of manuscripts/funding applications will take place in months 18-24.

